### Data management

4.4

All study data will be stored on the secure research drive of Amsterdam University Medical Center, in compliance with institutional data protection policies. Questionnaire data will be collected and managed through Castor. Paper questionnaires completed by older adults will be manually entered into Castor by researchers. Transcripts from interviews and focus groups will be coded and stored on the secure research drive, separately from participant identifiers. All data will be coded using a subject ID; the key linking subject IDs to participant identities will be stored separately and accessible only to authorized researchers. Data will be retained for a minimum of 10 years in accordance with institutional and regulatory guidelines. Secure data transfers will be managed via SURF FileSender.

## Discussion

5

This protocol presents the feasibility study of the Data Nurse intervention. This novel complex intervention combines person-centered shared decision-making with data-informed care to support independent functioning among older adults receiving district nursing care. To our knowledge, no intervention combining these two components has been previously developed or evaluated in this setting; however, they have been shown to be effective in other clinical settings.

The study has several strengths. The real-world implementation across multiple organizations increases the relevance of the findings for everyday district nursing practice. The mixed-methods approach combines validated instruments with in-depth qualitative exploration, allowing for comprehensive assessment of both process and preliminary outcomes. The involvement of data champions as local champions reflects implementation science principles for sustainable practice change (Pettersen et al., 2024), and responds to identified needs for organizational support when introducing data-informed practices in district nursing care (Veldhuizen et al., 2024a). The dual stakeholder perspective, assessing outcomes from both team members and older adults, recognizes that feasibility depends on the experiences of all involved. Finally, the study prioritizes contextual factors and participant experiences over formal hypothesis testing, in line with Medical Research Council guidance for evaluating complex interventions in their early stages (Skivington et al., 2024).

### Limitations and challenges

5.1

Several limitations should be acknowledged. The non-randomized design may introduce selection bias, though this reflects the operational constraints of district nursing practice and is consistent with recommendations for feasibility studies (Eldridge et al., 2016). Self-reported fidelity measures may be subject to social desirability bias, which will be mitigated through triangulation with team logbooks and structured monthly meetings. The five-month intervention period may be insufficient to capture the full adoption of a complex behavioral intervention. The comparability of the selected domains of the TOPICS-SF data between groups warrants attention, as the instrument is administered through different channels. Finally, the limited number of clusters may constrain the statistical analysis of secondary outcomes. The findings will inform whether the intervention warrants a larger effectiveness trial, which components require refinement, and what implementation strategies are needed across district nursing contexts.

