### Primary outcomes

3.14

Primary outcomes concern feasibility, acceptability, fidelity, barriers and facilitators, and experiences related to the Data Nurse intervention. These outcomes will be assessed using a mixed-methods approach combining quantitative instruments and qualitative data collection.

**Feasibility** refers to the extent to which the intervention can be successfully used or carried out by the intended users in routine district nursing practice. Feasibility will be measured in district nursing team members and older adults from the intervention group using the Feasibility of Intervention Measure (FIM), a five-item Likert scale assessing perceived implement ability (Weiner et al., 2017). The feasibility of the two components of the total intervention will be assessed in team members; the feasibility of the patient preparatory tool shared decision-making will be assessed in older adults.

**Acceptability** concerns the degree to which nursing professionals and older adults consider the intervention appropriate, relevant, and worthwhile (Sekhon et al., 2017). Acceptability will be measured in nursing professionals and older adults from the intervention group using a questionnaire based on the Theoretical Framework of Acceptability (TFA), assessing affective attitude, perceived burden, ethicality, coherence, perceived effectiveness, self-efficacy, and opportunity costs on a 5-point Likert scale (Sekhon et al., 2017). The acceptability of the total intervention will be assessed in nursing professionals; the acceptability of the patient preparatory tool shared decision-making will be assessed in older adults.

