**Fidelity** addresses whether the intervention is delivered as intended, including completion of training, use of the shared decision-making approach and patient preparatory tool shared decision-making, and dashboard engagement. Fidelity will be measured in nursing professionals from the intervention group using self-developed questionnaires (Supplementary File 3), tracking adherence indicators such as e-learning completion, use of stepwise person-centered shared decision-making from the e-learning, patient preparatory tool shared decision-making usage, and dashboard interactions. Teams complete these questionnaires on Castor one week before monthly online fidelity meetings with researchers, data champions, and team leaders. During these meetings, participation and delivery will be discussed using the Kotter framework (Kotter, 1996). Team logbooks will be used to document participation and implementation challenges throughout the intervention period, complementing the structured meeting discussions. Fidelity is considered high when ≥80% of teams completed the planned activities, consistent with commonly used thresholds for high intervention fidelity in implementation research (Borrelli, 2011).

**Barriers and facilitators** are factors that hinder or support the implementation of an intervention, encompassing motivation, capability, organizational readiness, and context (Huijg et al., 2014). Barriers and facilitators will be identified among nursing professionals in the intervention group using the Theoretical Domains Framework (TDF) questionnaire, covering these domains on 5-point Likert scales (Huijg et al., 2014).

**Experiences** will be measured regarding how nursing professionals and older adults perceive and reflect on working with the intervention in daily practice, including how it fits within existing workflows, how it shapes conversations and decision-making with older adults, and what unexpected effects, learning points or adaptations emerge during use. This compliments the other primary outcomes by providing in-depth, contextualized insights that cannot be caputered through standardized scales such as FIM, TFA en TDF.

A self-developed questionnaire captures nursing professionals' experiences with using the stepwise person-centered shared decision-making method in practice (supplementary file 4.).

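### Team logbooks and monthly meetings appear to share informants and audience with the fidelity questionnaire, so they cannot be relied on to reduce its self-report bias, and one over-reporting team can change the fidelity label

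*Protocol article*

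**What the plan says.** Section 3.14 (Primary outcomes) lists fidelity among the primary outcomes: "Primary outcomes concern feasibility, acceptability, fidelity, barriers and facilitators, and experiences related to the Data Nurse intervention". The instrument is self-report: "Fidelity will be measured in nursing professionals from the intervention group using self-developed questionnaires". The adherence indicators are e-learning completion, use of the stepwise conversation method, "patient preparatory tool shared decision-making usage, and dashboard interactions".

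On the reporting route, the section states: "Teams complete these questionnaires on Castor one week before monthly online fidelity meetings with researchers, data champions, and team leaders". On the logbooks it states: "Team logbooks will be used to document participation and implementation challenges throughout the intervention period, complementing the structured meeting discussions". The success criterion is: "Fidelity is considered high when ≥80% of teams completed the planned activities".

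Table 1 gives only the self-developed questionnaire and the monthly meetings under fidelity. Section 5.1 (Limitations and challenges) then concedes that self-reported fidelity is open to social desirability bias, "which will be mitigated through triangulation with team logbooks and structured monthly meetings".

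**The concern.** Triangulation reduces a bias only when the second source does not share it. Here a team that wishes to look compliant can do so in the questionnaire, in its logbook and in the meeting. Agreement among the three would then show that the team is consistent, not that it delivered the intervention. Section 5.1 nevertheless presents the agreement as a remedy, so readers may discount a bias that has not been addressed.

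Fidelity is also the only primary outcome for which the article states a numerical threshold. Section 5.1 says the findings will inform whether a larger trial is warranted and which components need refinement. If delivery is overstated, disappointing results are more easily blamed on the intervention than on how it was delivered.

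**Working it through.** **Step 1. Who supplies each source, and to whom**

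- Questionnaire: intervention-team professionals, through Castor, ahead of the meeting with researchers (3.14).
- Monthly meeting: team leaders and data champions, with researchers (3.14, Table 1).
- Logbook: described as the team's own. That the team writes it is implied, not stated (3.14).
- Relationship: researchers also support team leaders and data champions through monthly contact (3.7).

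No source from outside the teams is named for fidelity. The paragraph in 3.14 on focus groups and interviews opens by covering all primary outcomes, but its list of topics omits fidelity.

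**Step 2. The threshold in whole teams**

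The abstract gives 14 teams, 8 of them intervention teams. Section 3.17 is worded as if each organization contributed 14, but its own total confirms 14 overall: 14 × 12 = 168 professionals.

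- 0.80 × 8 = 6.4, so at least 7 teams are needed.
- 6/8 = 75%: not high.
- 7/8 = 87.5%: high.

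**Step 3. How easily over-reporting changes the label**

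The article gives no over-reporting rate, so one must be assumed. Let t be the number of teams that truly completed the activities, and f the chance that a non-completing team reports completion. Assume that teams report independently and that true completers always say so. Then

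P(false high) = P(Binomial(8 − t, f) ≥ 7 − t)

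- For t = 6 this is 1 − (1 − f)².
- For t = 5 this is 3f²(1 − f) + f³.

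| f (assumed) | t = 6 | t = 5 |
|---|---|---|
| 0.1 | 19% | 3% |
| 0.2 | 36% | 10% |
| 0.3 | 51% | 22% |
| 0.5 | 75% | 50% |

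**Step 4. Which indicators have a record other than the teams' report**

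- Preparatory tool: yes. It is the intervention group's source for the TOPICS-SF items (3.15, 3.18.1.2), older adults' paper forms are entered by researchers (3.18.1), and participants are registered in Castor (3.10). Numerator and denominator are therefore already collected.
- E-learning and dashboard: both are digital, and the dashboard was developed in Qlik Cloud (3.4). The article mentions no completion records or access logs, so their availability is an assumption.
- Stepwise conversation and team reflection sessions: no such record is shown.

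**The case against.** The strongest reply is that section 5.1 discloses the limitation, says only that bias is possible, and claims to lessen it, not to remove it. Logbooks kept throughout the period can contradict a monthly questionnaire, and the questionnaire itself (Supplementary File 3) is not shown. This stands as far as it goes: the sources can catch errors of recall and inconsistencies. It does not show that they reduce a bias that all three may share.

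A second reply is that older adults also supply evidence, through the FIM and TFA on the tool and through interviews, and that section 4.3 integrates these. The two questionnaires rate feasibility and acceptability, not whether the team delivered the activities, and fidelity is missing from the interview topics.

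Three cautions about the remedy also stand:

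- Staff may use the dashboard and e-learning while declining data collection (3.8), and consent precedes data collection (3.12). Usage exports could therefore include people who did not consent.
- Returned tools show completion among enrolled older adults, not that the tool was discussed. Team leaders make the Castor registrations, so the denominator is not wholly independent of the teams.
- Judging fidelity on records alone would leave out the shared decision-making conversation, which is central to the intervention.

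Finally, no progression rule is attached to the high-fidelity label, and fidelity is analysed descriptively (4.2). This limits the consequence.

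**Conclusion.** The assurance in section 5.1 is not supported by the sources it names. The fidelity result remains exposed to social desirability bias, probably upward and of unknown size. One over-reporting team is enough to change the label when exactly 6 of the 8 teams truly completed the activities. In that case the chance of a false high label runs from 19% to 75% as f goes from 0.1 to 0.5. If 5 truly completed, it runs from 3% to 50%. These figures rest on the assumed f and on independent reporting by teams. That the logbooks share the teams' viewpoint is inferred from their description.

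A reader might infer three stronger things that the article does not support:

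- That the result is known to be biased. Only exposure to bias can be shown.
- That objective records are at hand for most indicators. This is documented only for the preparatory tool.
- That the 80% label decides whether the programme goes forward. The findings as a whole are said to inform that, and no rule ties it to fidelity.

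**What to change.** In section 3.14:

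- Take preparatory-tool use per team as completed tools received divided by older adults registered in Castor. Count the tool completed before the initial care conversation, not the close-out TOPICS-SF measurement in Table 1.
- Use this ratio in place of the team's own report of tool use, or as a cross-check on it, when that indicator is judged against the 80% rule. State what share counts as completed for a team before the counts are examined.
- Add e-learning and dashboard usage as team-level aggregates only where the records can be obtained and their use fits the consent given.
- Keep the stepwise conversation and the reflection sessions in the fidelity verdict, labelled as self-report only.

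In section 5.1, replace the claim of mitigation with a statement that logbooks and meetings check consistency but do not remove the bias. Add that the tool ratio shows completion among enrolled participants, not discussion of the tool in the conversation.

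The cost is a small amount of counting from data already collected and a few sentences of text. No new assessors are needed. Usage records would need a request to the platform holders and a check against consent.

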## Conclusions

6

This feasibility study will provide essential evidence on the feasibility and preliminary results of the Data Nurse intervention, a novel complex intervention combining person-centered shared decision-making with data-informed care to support independent functioning among older adults receiving district nursing care. Findings will inform intervention refinement.

## Data statement

The datasets generated and/or analysed during this study will not be publicly available due to the sensitive nature of the data and the need to protect participant confidentiality. Data will be available upon reasonable request, following publication of the study results, subject to ethical approval and the signing of a Data Sharing Agreement (DSA). Requests for data access should be directed to the corresponding author. Data will be retained for a minimum of 10 years in accordance with institutional guidelines of Amsterdam UMC.

## Study status

Study initiation commenced on June 2025. Recruitment and inclusion of district nursing teams took place in June 2025. Patient recruitment and inclusion will occur between June 15th and the end of September 2025. Qualitative analysis of interview and focus group data will be conducted from November to April 2026. Quantitative data analysis, including patient-reported outcome measures (PROMs) and care metrics, will be carried out between November 2025 and April 2026.

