**Registration:**

Trial registration: ISRCTN, 14972807, registered [8 December 2025], first participant recruited [4 June 2025].

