**Enrolment**										
	Eligibility screening	DNT members		**X**						
	Informed consent	DNT members + older adults		**X**						
	Baseline data collection	DNT members			**X**					
	Baseline data collection	Older adults			**X**					
	Allocation	DNT			**X**					

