**Intervention or comparator**										
	Data Nurse intervention cycle*	DNT member (I)			**X**	→	→	→	→	
	Care as usual	DNT members (C)			**X**	→	→	→	→	

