##### Older adults

3.18.1.2

At baseline, characteristics of older adults who participate will be collected. These include year of birth, gender, marital status, living situation, highest level of education completed, country of birth, reason for receiving care, frequency of contact with district nursing, financial concerns, and care or support from the municipality. Additional qualitative information will be collected on older adults' living situation and municipal support.

Older adults in the intervention group will complete the patient-shared decision-making preparatory tool, based on the TOPICS-SF and covering self-reported independent functioning, general health, pain, emotional well-being, social activities, quality of life, and personal goals and wishes. In addition, they will complete the TFA questionnaire on acceptability of the patient preparatory tool shared decision-making and the CollaboRATE questionnaire on patient-reported involvement in shared decision-making. Individual interviews will be conducted to explore their experiences with person-centered shared decision-making.

Older adults in the control group will complete selected domains of the TOPICS-SF, specifically the self-reliance domain (10 items) and the social activities domain (1 item, to measure self-reported independent functioning, as well as the CollaboRATE questionnaire.

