### Quantitative analysis

4.2

Paper questionnaires will be manually entered into Castor to ensure a complete central database. Data will be checked for outliers, inconsistencies, and missing values prior to analysis. Likert scale responses will be treated as ordinal variables. All statistical analyses were conducted using R, version 4.4.3, an open-source software environment for statistical computing and graphics (Posit team, 2025). Demographic characteristics of participants will be summarized using descriptive statistics (means, standard deviations, frequencies, and percentages). Primary outcomes, including feasibility (FIM), acceptability (TFA), fidelity, and barriers and facilitators (TDF), will be analyzed descriptively. Retention and participation rates will be calculated as percentages of initial enrolment to assess engagement throughout the study. For secondary outcomes (self-reported independent functioning, patient-reported shared decision-making, and nursing care delivery patterns), changes between baseline and follow-up will be explored descriptively. Effect sizes and confidence intervals will be reported to inform the design of a future effectiveness trial.

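### Table 1 puts older adults' consent in May and their only baseline in June, but Study status recruits them until the end of September, so later baselines in intervention teams follow the team's start and follow-up varies from about 1.1 to 5.5 months

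*Protocol article*

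**What the plan says.** Table 1 (section 3.18.1) has calendar-month columns from May to November.

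- **Consent:** one mark, in May, for "DNT members + older adults".
- **Baseline:** the row "Baseline data collection" for older adults has one mark, in June, the same column as team allocation.
- **Intervention:** the "Data Nurse intervention cycle" starts in June, with arrows through October. The e-learning and dashboard workshop are also in June.
- **Secondary outcomes:** TOPICS-SF and CollaboRATE are marked in June and November only.

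The Study status section gives other dates. On teams: "Recruitment and inclusion of district nursing teams took place in June 2025". On older adults: "Patient recruitment and inclusion will occur between June 15th and the end of September 2025". The registration line in the abstract reads "first participant recruited [4 June 2025".

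Section 3.8 says that all members of intervention teams use the tools in usual practice, and that eligible older adults are already in care. Section 3.15 takes TOPICS-SF in the intervention group through the preparatory tool, which section 3.10 hands out ahead of the person's initial conversation. For the secondary outcomes, section 4.2 states that "changes between baseline and follow-up will be explored descriptively", with effect sizes and confidence intervals to inform a later trial.

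**The concern.** Table 1 is the SPIRIT schedule, so readers will take it as the design: consent before allocation, one common baseline, and about five months to follow-up. The recruitment dates describe something else. Older adults join over three and a half months, in or after the month in which their team was allocated, and are approached by team members.

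Two consequences bear on the secondary outcomes. First, a person enrolled in August in an intervention team belongs to a caseload already served by staff using the method. CollaboRATE asks about shared decision-making in the clinical encounter. If the encounter rated at baseline took place after the team started, part of the effect is already in the baseline. Control baselines are late too, but unexposed, so the problem affects one arm only. Second, a fixed close-out gives early and late recruits very different follow-up and exposure, and section 4.2 does not separate them. If the arms recruit at different speeds, the mix of intervals will differ between arms. At stake are the effect sizes and confidence intervals offered as planning figures for the next trial.

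**Working it through.** **The plan's own figure.** Section 3.18.1 gives data collection as five months, June to November 2025. From 1 June to 1 November is 153 days; 153 / 30.4375 = 5.03 months. The figure reproduces for the study calendar, but it is not each older adult's follow-up.

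**The two schedules side by side.**

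| Item | Table 1 | Study status and registration line |
|---|---|---|
| Older adults' consent | May | 15 June to end of September |
| First recruitment of any participant | May implied | 4 June |
| Older adults' baseline | June only | No earlier than enrolment, so up to end of September |
| Team inclusion / allocation | Allocation in June | Teams included in June |

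A May consent is incompatible with both the 4 June and the 15 June date. A June baseline is impossible for anyone enrolled from July on.

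**Recruitment window.** 15 June to 30 September inclusive is 16 + 31 + 31 + 30 = 108 days. Days after June: 31 + 31 + 30 = 92. 92 / 108 = 85%.

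**People affected.** The expected sample is 210 to 294. The accrual pattern is not stated, so this is a range over assumptions:

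| Share enrolled after June (assumed) | Number without a possible June baseline |
|---|---|
| 25% | 53 to 74 |
| 50% | 105 to 147 |
| 85% (even accrual) | 179 to 250 |

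**Follow-up to close-out.** Table 1 gives only the month, so the first and last day of November are the limits.

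| Enrolled | To 1 November | To 30 November |
|---|---|---|
| 15 June | 139 days = 4.6 months | 168 days = 5.5 months |
| 30 September | 32 days = 1.1 months | 61 days = 2.0 months |

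The overall range is about 1.1 to 5.5 months.

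**Exposure.** The team's start is dated only to June. When the last older adult enrols on 30 September, an intervention team has been delivering for 92 days (start 30 June, 3.0 months) to 121 days (start 1 June, 4.0 months). That last recruit has 31 days until the end of October, the last month with an arrow in Table 1.

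**Which baselines are exposed.**

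- *Intervention team, July to September:* after the team's start. CollaboRATE is the more exposed. TOPICS-SF is less so, because it is taken in the tool ahead of the person's initial conversation.
- *Intervention team, 15 to 30 June:* ambiguous, since the start date within June is not given.
- *Control team:* late, but unexposed.

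**The case against.** The best reply is that little depends on this. Section 3.13 calls all effectiveness outcomes exploratory, without formal hypothesis testing, and section 4.2 analyses them descriptively. The primary outcomes concern use of the intervention, are collected in the intervention group only, and do not rest on these change scores. That stands, and it limits the severity. Section 5.1 also admits selection bias from non-randomization, and section 3.18 says openly that team members recruit from their caseload. It does not, however, mention late baselines or unequal follow-up.

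Some stronger readings are tempting but unsupported:

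- *A percentage for the lost effect.* This would need the accrual pattern, the share of the effect that comes from trained staff rather than the tool, and whether each late recruit had already had such a conversation. None is stated. A July recruit's baseline may still describe care before training.
- *Every baseline follows the intervention's start.* This cannot be said for 15 to 30 June, nor for controls.
- *CollaboRATE is completed after the tool.* Section 3.18.1.2 says "Older adults in the intervention group will complete the patient-shared decision-making preparatory tool" and then adds further questionnaires. That is a list of instruments, not an order.
- *The November contrast should replace the change score.* Organizations allocated teams by availability, staffing and time (section 3.9). Dropping baseline information would exchange possible attenuation for confounding.

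**Conclusion.** The contradiction between Table 1 and Study status is certain, and the two must be reconciled. If the Study status dates hold, follow-up ranges from about 1.1 to 5.5 months (assuming the November close-out applies to everyone), and 85% of the recruitment days fall after the only baseline month in Table 1. The share of people affected is unknown. For July to September recruits in intervention teams, the baseline falls after the team's start. The CollaboRATE change may therefore be biased towards no effect, by an amount the document does not allow one to calculate. TOPICS-SF is less exposed. This is a should-fix: it leaves the primary feasibility outcomes intact but makes the effect sizes meant for the next trial hard to interpret.

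**What to change.** 1. Correct Table 1 so that older adults' consent and baseline occur at individual enrolment, 15 June to 30 September, after team allocation; or correct Study status if those dates are wrong.
2. Define baseline relative to each person's enrolment and their team's start date, with CollaboRATE and TOPICS-SF taken before that person's first shared decision-making conversation under the intervention. Where data are already collected, use this definition to classify each baseline.
3. Report the enrolment-to-follow-up interval by arm. Show the secondary outcomes by enrolment month, or by enrolment before versus after team start, and adjust the effect sizes for the interval.
4. Present the November between-group difference, adjusted for available baseline characteristics, alongside the change score and not in place of it.
5. State the late baselines and unequal exposure as a limitation in section 5.1.

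The cost is a table correction, some wording and a little more analysis. Steps 3 to 5 remain possible after data collection. They require retrievable enrolment dates. The article says that older adults are registered in Castor but does not say that a date is recorded, so the dates may have to come from registration or consent records.
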